### Intervention

2.6

#### FIRM group

2.6.1

FIRM is an intensive integrated care program carried out by a rehabilitation physician, physical therapist, occupational therapist, nutritionist, clinical nurse specialist, and social worker. It sets PT and OT goals, retrains physical independence, and includes detailed discharge planning (Table 1). It consists of total 10 days’ PT sessions (twice per day for 60 min) and 4 days’ OT sessions during the 2 weeks after surgery. PT (weight-bearing, strengthening, gait training, aerobic, and functional exercises) was gradually increased based on the patient's functional level. OT involving training to perform activities of daily living (ADLs; transfer, sit to stand, bed mobility, dressing, self-care retraining, and using adaptive equipment) was provided. Intensive patient education by multidisciplinary rehabilitation members was also provided.

**Table 1 T1:**
[figure not shown]
Fragility fracture integrated rehabilitation management.

#### Conventional group

2.6.2

Conventional postoperative rehabilitation involves PT (once per day for 30 min), fall prevention, and discharge planning, including in-hospital, postoperative usual orthopedic care. The PT sessions will be the same as provided to the FIRM group.

#### Control group

2.6.3

This group will consist of an age- and sex-matched historically controlled cohort. Participants will be discharged without having received PT during the postoperative hospitalization period. The aim will be to determine the natural course of the patients’ functional status.

### Outcome measures

2.7

The following demographic data will be collected at baseline: age, sex, fracture location and laterality, type of surgery, and underlying disease. Functional outcomes will be measured at 1 (before intervention) and 3 weeks (after 2 weeks’ intervention), 3, 6, and 12 months after operations.

The primary outcome of this study will be Koval walking ability scores^[11]^ (range: 1–7; with a higher score indicating a worse outcome), which rates physical functioning according to walking dependency. The secondary outcomes will be as follows: physical functioning and walking ability, assessed according to the functional ambulatory category^[12]^ (range: 0–5; a lower score indicates a worse outcome) and the modified Rivermead mobility index^[13]^ (range: 0–40; a lower score indicates a worse outcome); balance and fall risk, assessed using the Berg balance scale^[14]^ (range: 0–56; a lower score indicates a worse outcome); cognition, evaluated using the Korean version of the Mini-Mental State Examination^[15]^ (range: 0–30; a lower score indicates a worse outcome); mood, evaluated using the Korean version of the Geriatric Depression Scale^[16]^ (range: 0–30; a lower score indicates a worse outcome); quality of life (QOL), evaluated using the Euro Quality of Life Questionnaire 5-dimensional classification^[17]^ (EQ-5D; range: 0–1; a lower score indicates a worse outcome); ADLs determined using the Korean version of the modified Barthel index^[18]^ (range: 0–100; a lower score indicates a worse outcome) and the Korean version of the Instrumental ADL^[19]^ (range: 0–3; a higher score indicates a worse outcome); and frailty assessed based on fatigue, resistance, ambulation, illnesses, and loss of weight (FRAIL) using the Korean version of the FRAIL scale^[20]^ (K-FRAIL; range: 0–5; a lower score indicates a worse outcome). Functional assessments will be conducted with the control group via telephone surveys performed at the same time points but measures will be limited to the Koval and EQ-5D. The adherence and drop-out rates of the program will be monitored during stage 2, in which FIRM will be applied in the community-based hospital system. Each researcher charged with outcome evaluation at each of the 3 core hospitals will work on standardizing all measuring protocols by arranging a consensus meeting before the start of the study. Regular meetings to discuss ways to unify the measurement methods will then be held.

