### Background

1.1

Although the quality of the surgical and perioperative treatment of hip fracture has improved,^[1]^ the physical and functional recovery after surgery and acute care remains deficient. Before hip fracture, 11% of community-dwelling elderly individuals are bed-ridden and 16% are in long-term-care facilities.^[2]^ Within 1 year after sustaining a hip fracture, individuals experience is a very serious decrease in the quality of their life, and the mortality rate in this group is as high as 36%.^[3]^ A cohort study with the Norwegian Hip Fracture Register (n = 10,325) showed that 58% and 59% of patients had walking problems and pain, respectively, after 12 months of follow up.^[4]^ The high rates of morbidity and mortality after hip fracture have increased the cost of medical care and thus also constitute a serious socioeconomic problem. In Europe, the estimated economic burden imposed by fragility fractures in 2010 was €37 billion, with a 25% increase in the cost expected by 2025.^[5]^ Therefore, it is important to provide multidisciplinary and comprehensive rehabilitation aimed at restoring the patient to preoperative physical functioning after surgery for hip fracture.

Comprehensive rehabilitation after hip fracture usually consists of physical therapy (PT), occupational therapy (OT), fall prevention, nutritional support, psychiatric evaluation, complication care, and discharge planning with environmental modification.^[6]^ In a single-center controlled trial of hip fracture patients 70 years of age or older (n = 1077), comprehensive geriatric care was shown to improve mobility compared with the usual orthopedic care at 4 months.^[7]^ A Taiwanese study compared 3 groups of elderly patients (n = 229) with hip fracture treated with different approaches: usual care, interdisciplinary care (geriatric consultation, continuous rehabilitation, and discharge planning), and comprehensive care (interdisciplinary care plus nutrition consultation, depression management, and fall prevention).^[8]^ This research found a lower risk of depression and malnutrition in the comprehensive care group than in the interdisciplinary care group 1 year after discharge. Therefore, better functional outcomes can be expected following the provision of a comprehensive postoperative rehabilitation program to hip fracture patients.

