### Data analysis

2.8

Data will be collected using a standardized data entry form and entered into the data management system. The intention-to-treat principle will be used for data analysis. Participant characteristics will be described using means and standard deviations for continuous data and frequencies and percentages for categorical data. The 3 groups will be compared using an analysis of variance (ANOVA) or the nonparametric equivalence Kruskal–Wallis test if required. To compare paired data (intragroup) between 2 different points, we will use repeated-measures ANOVA and Friedman tests for continuous and nonparametric data, respectively. Statistical significance will be defined as a *P* value < .05. All statistical analyses will be performed using SPSS version 19.0 for Windows (IBM Corp, Chicago, IL).

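### The listed baseline data hold no pre-fracture walking grade, and the group comparison names no adjustment even for the 1-week Koval: lost precision for FIRM versus conventional, possible bias against a historical control

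*Protocol article*

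**What the plan says.** Section 2.7 (Outcome measures) gives the baseline list: "The following demographic data will be collected at baseline: age, sex, fracture location and laterality, type of surgery, and underlying disease". The next sentence gives the functional schedule: "Functional outcomes will be measured at 1 (before intervention) and 3 weeks (after 2 weeks’ intervention), 3, 6, and 12 months after operations". Koval is then named as primary: "The primary outcome of this study will be Koval walking ability scores", on a scale of 1 to 7 where higher is worse. The earliest Koval is therefore post-operative but precedes the intervention. The control group is assessed "via telephone surveys performed at the same time points but measures will be limited to the Koval and EQ-5D", so it has a 1-week Koval too.

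Section 2.6.3 describes the control group: "This group will consist of an age- and sex-matched historically controlled cohort". Section 2.8 (Data analysis) gives the between-group analysis: "The 3 groups will be compared using an analysis of variance (ANOVA) or the nonparametric equivalence Kruskal–Wallis test if required". It names no covariate.

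Section 1.1 (Background) gives the rationale as "rehabilitation aimed at restoring the patient to preoperative physical functioning after surgery for hip fracture", and the Abstract says the same in substance. Section 1.2 (Objectives) is framed as a comparison of effectiveness. Section 2.2 sets no eligibility limit on walking ability before the fracture.

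**The concern.** The primary outcome is a walking grade, and walking before the fracture is a natural predictor of walking after it. Eligibility does not restrict prior ability, and section 1.1 itself reports that, before hip fracture, 11% of community-dwelling elderly people are bed-ridden and 16% are in long-term care. Prior ability can thus be expected to vary widely, yet the listed data do not capture it.

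Three things are at stake:

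- **Precision, FIRM versus conventional.** The stated test leaves prognostic variation in the error term.
- **Bias against the control.** If the control is a historical cohort, age and sex matching does not equalize prior walking, and the unadjusted test does not remove a difference.
- **The restoration question.** Return to the pre-fracture level motivates the programme but cannot be assessed from the data listed.

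**Working it through.** **Inputs from section 2.3:** SD 1.075, difference 0.5 grade, two-sided alpha 0.05, at least 80% power, 85 per group.

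**The plan's own figure.** The two-sample formula gives n = 2 × (1.960 + 0.842)² × 1.075² / 0.5² = 72.6, so 73 per group. Dividing by 0.864, the minimum asymptotic relative efficiency of a rank test, gives 84.5, so 85, which matches. That rank-test step is an assumption; the article does not state it. Nothing below depends on it.

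**Assumptions** (the document gives no correlations and no group gap):

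- Pre-fracture, 1-week and follow-up Koval have a common pairwise correlation r and equal SDs.
- 1.075 is the SD of a follow-up score.
- A parametric comparison is used, with normal approximations.
- The small loss of precision that comes from a covariate differing between groups is ignored.

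**Precision.** SE = (residual SD) × √(2/85); power = Φ(0.5/SE − 1.96).

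- Unadjusted: SE = 1.075 × 0.1534 = 0.1649; 0.5/0.1649 = 3.03; power 85.8% (85.4% with the t distribution).
- 1-week Koval as covariate: residual SD = 1.075 × √(1 − r²). At r = 0.5 this is 0.931, SE 0.1428, power 93.8%.
- Both covariates: R² = 2r²/(1 + r). At r = 0.5, R² = 0.333, residual SD 0.878, SE 0.1346, power 96.0%.

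| r | unadjusted | 1-week | 1-week + pre-fracture | extra effective n from the pre-fracture item |
|---|---|---|---|---|
| 0.3 | 86% | 89% | 90% | ×1.06 |
| 0.5 | 86% | 94% | 96% | ×1.13 |
| 0.7 | 86% | 99% | 99.7% | ×1.20 |

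The last column is (1 − r²)/(1 − R²). At r = 0.5 and above, most of the gain comes from the 1-week Koval, which is already collected.

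**Bias in the control contrast.** Let g be the pre-fracture gap in grades. With equal SDs the slope equals r.

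- Unadjusted bias = g × r. At g = 0.5, r = 0.5: 0.25 grade, half the 0.5 target. 0.25/0.1649 = 1.52, so with no true effect the test rejects 33% of the time.
- After 1-week adjustment, the 1-week scores differ by g × r and the covariate removes r times that, leaving g × r × (1 − r) = 0.125 grade. 0.125/0.1428 = 0.88; rejection rate 14%.
- Adding an error-free pre-fracture grade would remove this component of bias entirely.

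| g (r = 0.5) | bias, unadjusted | false positives | bias, 1-week adjusted | false positives |
|---|---|---|---|---|
| 0.25 | 0.125 | 12% | 0.063 | 7% |
| 0.5 | 0.25 | 33% | 0.125 | 14% |
| 1.0 | 0.50 | 86% | 0.25 | 42% |

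At g = 0.5, varying r from 0.3 to 0.7 moves the unadjusted rate from 15% to 57% and the 1-week-adjusted rate from 10% to 15%.

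**The case against.** The strongest case against has five parts.

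1. **This is a condensed article.** The list is introduced as demographic data, and section 2.8 refers to a data entry form that is not shown. A pre-fracture item may exist there. This stands as a limit: the point concerns the lists as printed. Those lists do, however, go beyond demography to surgery type and comorbidity, and the functional schedule is set out visit by visit.

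2. **A pre-intervention Koval exists.** This stands. A reader might infer that the trial has no usable baseline and cannot adjust for walking status at all. The documents do not support that: the 1-week score is available in all three groups and can carry much of the adjustment. What it cannot show is the level each patient had to regain, and section 2.8 does not name it as a covariate.

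3. **Restoration is not an endpoint.** This stands. A reader might infer that the trial fails its own objective. It does not: restoration is rationale, and section 1.2 asks for a comparison of effectiveness.

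4. **Randomization protects FIRM versus conventional.** This stands; there is no bias there. Planned power also exceeds 80% on the simple formula, so the precision gain mends no shortfall.

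5. **The bias belongs to the control design.** This stands in part. The Abstract and section 2.5 describe randomization to three groups, while sections 1.2, 2.1.1 and 2.6.3 describe a historical control. The bias arises only under the second reading, and prior walking is one of several possible differences, alongside era and telephone assessment.

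The SD is also uncertain. Section 2.3 reports 1.075 beside a mean difference, so it may be the SD of a change score, in which case the precision formulas would not apply as written.

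**Conclusion.** The point holds in a limited form. The listed data lack a pre-fracture walking grade, and the stated comparison leaves unused a pre-intervention Koval that the trial already collects.

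For FIRM versus conventional the cost is precision only: about 86% power unadjusted against 94% with the 1-week Koval and 96% with both, if all correlations are 0.5. For the control contrast, if that group is historical, an assumed 0.5-grade gap gives about 33% false positives unadjusted and about 14% after 1-week adjustment alone.

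It would be too strong to present the 33%, or the whole gain over an unadjusted test, as the price of omitting the pre-fracture item. Part of each is recovered by the 1-week score; at r = 0.5 the item itself adds an effective sample size of about ×1.13. All these sizes rest on assumed correlations and gaps. This is a worthwhile, inexpensive improvement and not a fatal defect.

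**What to change.** 1. In section 2.8, analyse follow-up Koval in a model with group and the 1-week Koval as covariate. This costs no data collection.
2. In section 2.7, add a pre-fracture Koval grade, recalled by patient or proxy, to the baseline list in all three groups, asked by telephone in the control group. If the data entry form already holds it, say so.
3. Use that grade as a further covariate and in the matching or adjustment of the control cohort. Return to the pre-fracture grade can then be reported descriptively.

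The cost is one question per patient and one model term. The drawback is recall or proxy error, which may differ between groups because controls are reached by telephone, so record who answered and how. The item will not remove other differences between a historical cohort and the randomized groups; the conflicting descriptions of how the control group is formed must be reconciled separately.

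### Section 2.7 gives K-FRAIL, and apparently the Geriatric Depression Scale, a score direction opposite to what the scale measures

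*Protocol article*

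**What the plan says.** The protocol article, section 2.7, gives a range and a direction for every outcome scale.

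- **Frailty** is "frailty assessed based on fatigue, resistance, ambulation, illnesses, and loss of weight (FRAIL"), and the direction is "K-FRAIL; range: 0–5; a lower score indicates a worse outcome".
- **Mood** is "evaluated using the Korean version of the Geriatric Depression Scale^[16]^ (range: 0–30; a lower score indicates a worse outcome").
- **Scales marked the other way.** The Koval primary outcome is given as "range: 1–7; with a higher score indicating a worse outcome" and the Instrumental ADL as "range: 0–3; a higher score indicates a worse outcome".

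Frailty and mood are both secondary outcomes. In the historical control group, which is followed by telephone, "measures will be limited to the Koval and EQ-5D", so these two scales exist only for the FIRM and conventional groups. No other section of the article corrects the two entries or mentions reverse scoring.

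**The concern.** The direction printed for K-FRAIL does not fit the components named beside it. The direction printed for the depression scale does not fit the scale's name. The phrase suits the mobility, balance and cognition scales around it, so it may simply have been repeated.

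The stated direction is what turns a difference in means into a statement of benefit or harm. Section 2.8 compares groups by ANOVA or Kruskal–Wallis, which show that groups differ but not which did better. Section 2.5 keeps the statistician blind under nominal group names through the analysis, so an implausible direction is less likely to be noticed from the results. Depression also belongs to the trial's rationale: section 1.1 cites a lower risk of depression and malnutrition under comprehensive care. A benefit of that kind under FIRM, read by the printed rule, would look like harm.

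**Working it through.** There is no stated figure to reproduce. The check compares each stated direction with what the document says the scale measures, and then asks what a reversed direction would change.

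**Step 1: list the secondary scales (section 2.7).** There are nine: functional ambulatory category, modified Rivermead, Berg, Mini-Mental State Examination, Geriatric Depression Scale, EQ-5D, modified Barthel, Instrumental ADL and K-FRAIL. Eight are marked lower-is-worse and one (Instrumental ADL) higher-is-worse. Of the eight, six measure an ability or a state of health (ambulation, mobility, balance, cognition, quality of life, daily activities), and the direction fits. The other two are named for a problem, frailty and depression. So 2 of 9 are in question.

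**Step 2: is lower-is-worse a common convention?** No. Koval and Instrumental ADL keep higher-is-worse in the same paragraph, so direction is set scale by scale.

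**Step 3: K-FRAIL.** Five components on a 0–5 range imply one point per component. Fatigue, illnesses and loss of weight are plainly adverse, so the natural reading is a count of problems: 0 = none present, 5 = all present. Under the printed rule the patient with none would be the worst case and the patient with all five the best.

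**Step 4: Geriatric Depression Scale.** The document gives the name, the range and the direction, but no items, key or cut-off. By the name, more points should mean more depression. That is an inference from the name and not a contradiction with a described scoring rule.

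**Step 5: what does reversing a scale change?** Let x be a score on a scale from 0 to M (M = 5 or 30), and let x′ = M − x.

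- Mean difference, FIRM minus conventional: d′ = (M − mean₁) − (M − mean₂) = −d. Only the sign changes.
- ANOVA: variances within groups are unchanged and deviations between groups change sign. They enter F as squares, so F′ = F.
- Kruskal–Wallis: each rank R becomes N + 1 − R, where N is the number of patients. Deviations of mean ranks change sign and are squared, so H′ = H.
- The repeated-measures ANOVA and Friedman tests within groups are unchanged for the same reasons.

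The P value is therefore the same under either direction. What moves is which group, or which time point, is called better.

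**The case against.** The strongest objection is that nothing in the plan puts the printed directions to work. The document describes no composite, responder definition, one-sided test or decision rule that uses them. Section 2.7 also provides for a consensus meeting before the start, and regular meetings after it, to standardise measurement. Evaluators who follow the instruments' own scoring would not be misled by a parenthesis in an article. This part stands: the reversal depends on the printed direction being used, and the document does not show that it is.

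The evidence also differs between the two scales. For K-FRAIL the document does not itself use the word deficit, and resistance and ambulation are named as neutral functions, so the count of problems is still an inference. It is a strong one, given the other three components and the match between five components and a 0–5 range. For the depression scale the scoring source is not shown and the case rests on the name alone. It should be put as a query to be settled from the scoring sheet.

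The article format is not an answer. A condensed article may leave out a scale's direction, but here a direction is printed and conflicts with the text beside it.

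**Conclusion.** The K-FRAIL direction is wrong as written, judged on the document's own description of the scale. The depression-scale direction is very probably wrong, subject to a check of the Korean version. The reach is two of nine secondary scales, in the FIRM versus conventional comparison only.

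A reader might infer more, and the document does not support it:

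- **That the trial will report benefit as harm.** This follows only if the printed directions are used for coding or interpretation.
- **That significance or power is affected.** Reversal leaves the P values unchanged. The Koval primary outcome is marked higher-is-worse, and the sample size (85 per group, 282 recruited in total) is based on it.
- **That the registry entry or the analysis programs carry the error.** Neither is shown.

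The conclusion assumes that K-FRAIL gives one point per problem present and that the depression scale rises with depressive symptoms. The scoring sheets will settle both.

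**What to change.** Check the K-FRAIL and Geriatric Depression Scale entries against the scoring sheets of the Korean versions used. Once confirmed, change both phrases in section 2.7 so that a higher score indicates a worse outcome. Then confirm that the outcome coding used in the analysis has the same direction. If either scale is deliberately reverse-scored in this trial, say so in section 2.7 instead.

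The cost is two corrected phrases and one coding check. Sample size, tests and data collection stay as they are.

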**Methods and analysis::**

Elderly patients will be randomly assigned to either the FIRM, conventional, or control group for a 2-week intervention period following hip fracture surgery. The primary outcome of this study is Koval walking ability. All functional outcomes will be measured 1 and 3 weeks, 3, 6, and 12 months after the surgical intervention. Researchers will be blind to group allocation, and participants will be blind to outcome. A sample size of 282 participants will be necessary to demonstrate the effect of the FIRM program. After the RCT has been conducted in 3 core hospitals, FIRM will be applied in 6 community-based local hospitals to investigate the feasibility of the program. The data will be analyzed using the intention-to-treat principle.

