### Randomization and blinding procedure

2.5

Participants will be randomly assigned to 1 of the 3 groups using a computerized random number generator. The principal researcher will be blind to group allocation. Blinding will be initiated by a research associate implementing the randomization process described above. The associate researchers in the 3 hospitals will notify each participant's therapist of group allocation, enabling the therapist to implement the assigned rehabilitation protocol while maintaining the blinding of the other researchers. The principal researcher and the statistician will continue to be blind to group allocation, with the nominal group names assigned by the research associate maintained throughout data analysis. Outcome variables will be measured by researchers who are not involved in patient allocation. It is impossible to blind either the therapists conducting the interventions or the participants to group allocation. Nonetheless, only after their participation in the study is over will the patients be notified of the results and outcome measures.

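### In comparisons with the control group, the primary outcome is collected in a different way from the other two arms, and the blinding claims cannot extend to that group

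*Protocol article*

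**What the plan says.** Protocol article, section 2.7 (Outcome measures), on the primary endpoint: "The primary outcome of this study will be Koval walking ability scores". The scale runs from 1 to 7 and higher is worse. Time points are 1 week (before the intervention), 3 weeks, and 3, 6 and 12 months.

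The same section makes an exception for one arm: "Functional assessments will be conducted with the control group via telephone surveys performed at the same time points". It adds that for this group "measures will be limited to the Koval and EQ-5D". The other two arms receive the full battery, which includes a physical performance test: "balance and fall risk, assessed using the Berg balance scale". On who measures: "Each researcher charged with outcome evaluation at each of the 3 core hospitals will work on standardizing all measuring protocols".

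Section 2.8 (Data analysis) compares the 3 groups in one ANOVA or Kruskal–Wallis test. It does not say whether raw scores or changes from the 1-week value are compared.

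On blinding, the Abstract says: "Researchers will be blind to group allocation, and participants will be blind to outcome". Section 2.5 says: "Outcome variables will be measured by researchers who are not involved in patient allocation" and "The principal researcher and the statistician will continue to be blind to group allocation", the latter by means of nominal group names. The only exceptions it admits are therapists and participants.

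**The concern.** A walking grade obtained by telephone and one obtained by a hospital evaluator may differ systematically in the same patient. Here every control has the first kind and, it appears, every FIRM or conventional patient has the second. Among the planned data there is no patient in whom both are recorded and no arm in which they are mixed. A mode difference in the value analysed would therefore look like a treatment effect, or hide one, in any comparison that includes the control group. Because higher Koval grades are worse, telephone reports that are too favourable would hide a benefit over control, and reports that are too unfavourable would inflate it.

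Blinding is a second matter and does not depend on the size of any mode effect. If only controls are surveyed by telephone, the person conducting the survey knows the group. A dataset in which one group has two instruments and no others shows the statistician which group is control, whatever nominal name it carries.

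**Working it through.** **What the documents fix, side by side**

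| Item | FIRM and conventional | Control |
|---|---|---|
| Koval, EQ-5D | Evaluators at the 3 core hospitals; in-person assessment is inferred from the site evaluators and the Berg scale | Telephone survey |
| Other scales | Full battery | None |
| Group concealed from assessor | Claimed and possible | Not possible if only controls are telephoned |
| Group concealed from statistician | Possible between these two arms | Not possible, given the pattern of missing scales |

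Mode is thus a function of control versus non-control. It is the same in FIRM and conventional, so that contrast is free of it.

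**Illustration of size**

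The plan gives no figure for a mode effect, so there is none to reproduce. Inputs from section 2.3: n = 85 per group, SD = 1.075, two-sided 5% level, and planned values of 0.5, 0 and −0.5 grade for FIRM, conventional and control. The shift b is my assumption. It means a difference in the analysed value caused by mode alone, with no true group difference and groups otherwise comparable.

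Pairwise t-test:
- SE = 1.075 × √(2/85) = 0.165
- Noncentrality = b / 0.165, with 2 × 85 − 2 = 168 degrees of freedom
- b = 0.1, 0.2 and 0.3 give noncentrality 0.61, 1.21 and 1.82

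Three-group ANOVA with means (0, 0, −b):
- λ = 85 × (2b²/3) / 1.075²
- b = 0.1, 0.2 and 0.3 give λ = 0.49, 1.96 and 4.41

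Probability of P<.05:

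| Shift b (grade) | Pairwise with control, n = 85 | Pairwise with control, n = 94 | 3-group ANOVA, n = 85 |
|---|---|---|---|
| 0 | 5% | 5% | 5% |
| 0.1 | 9% | 10% | 9% |
| 0.2 | 23% | 25% | 22% |
| 0.3 | 44% | 48% | 45% |

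Relative to the planned differences, shifts of 0.1, 0.2 and 0.3 are 20%, 40% and 60% of the conventional–control difference (0 − (−0.5) = 0.5). They are 10%, 20% and 30% of the FIRM–control difference (0.5 − (−0.5) = 1.0).

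**When an offset would cancel**

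Write a control patient's telephone value at time t as true value + m(t). The change from 1 week then contains m(t) − m(1 week). This is zero if m is constant over time, and not otherwise. If raw scores at a visit are compared, m(t) enters in full. Section 2.8 does not settle which of the two is analysed.

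**FIRM versus conventional**

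Both arms share one mode. A t-test for a 0.5-grade difference has 85% power at 85 per group and 89% at 94, so this contrast can stand without the control group.

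**The case against.** The strongest reply is that the planned values of 0.5, 0 and −0.5 cannot be mean scores on a 1–7 scale and read most naturally as changes. Controls are to be surveyed at the same times as the others, including 1 week, so a constant offset would drop out of change from baseline. This stands as far as it goes, and it means bias is possible but not shown. It does not close the point: the analysis section does not commit to change scores, and nothing in the plan shows that a mode offset would stay constant.

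It is also true that the article nowhere says Koval is scored by observation in FIRM and conventional patients, or who makes the calls. Koval and EQ-5D could be taken by interview in every arm, which might make the mode difference smaller. In-person assessment is an inference, although singling out the control group for telephone surveys supports it.

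The size of any shift is an assumption, and at 0.1 grade the error rate rises only from 5% to 9%.

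The article does plan consensus and regular meetings to harmonise measurement. These align evaluators across hospitals. They do not produce Koval values collected by the same mode in all three groups, and a later analysis plan could not create those values either.

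A reader might infer that mode undermines every comparison in the trial, or that no analysis could remove it. The documents support neither: FIRM and conventional share one mode, and a constant offset would cancel in a change-score analysis.

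**Conclusion.** The point holds for FIRM versus control, conventional versus control and the 3-group test, and not for FIRM versus conventional. In those comparisons the mode of assessing the primary outcome is aligned with group, and the plan contains neither same-mode data nor a stated analysis that would remove a constant offset.

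If a shift of 0.1 to 0.3 grade reaches the analysed value, the false-positive rate in a pairwise control comparison is about 9% to 44% instead of 5%. That range rests on assumed shifts, on the SD of 1.075 applying to the analysed value, and on groups that are otherwise comparable. The last assumption is generous, because section 2.6.3 describes the control group as a matched historical cohort. That is a separate problem which matching the mode would not solve.

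The blinding statements in the Abstract and section 2.5 are too broad as written. They can hold between FIRM and conventional. They cannot hold for control, whatever the size of a mode effect.

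**What to change.** 1. Collect Koval and EQ-5D in FIRM and conventional patients by the same scripted telephone interview used for controls, at all five time points (1 and 3 weeks, 3, 6 and 12 months). The caller should not know FIRM or conventional allocation. Use only these telephone values for comparisons with control, and keep the hospital values for FIRM versus conventional. Covering all five points matters: calls at the later visits alone would leave no same-mode 1-week or 3-week value, and a change score would then mix modes in two arms but not in the third.
2. If that is not feasible, base the confirmatory conclusion on FIRM versus conventional and report all control comparisons as descriptive.
3. In either case, reword the Abstract and section 2.5 so that blinding of assessors, principal researcher and statistician is claimed only for FIRM versus conventional.

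Cost: two short instruments for up to 2 × 94 = 188 patients at 5 time points, at most 940 brief calls, with some added patient burden and staff time. Options 2 and 3 cost wording only. None of these changes makes the control group a randomised one.
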